## Abstract

**Introduction:**

Almost 60% of antibiotics in frail elderly are prescribed for alleged urinary tract infections (UTIs). A substantial part of this comprises prescriptions in case of non-specific symptoms or asymptomatic bacteriuria, for which the latest guidelines promote restrictiveness with antibiotics. We aim to reduce inappropriate antibiotic use for UTIs through an antibiotic stewardship intervention (ASI) that encourages to prescribe according to these guidelines. To develop an effective ASI, we first need a better understanding of the complex decision-making process concerning suspected UTIs in frail elderly. Moreover, the implementation approach requires tailoring to the heterogeneous elderly care setting.

**Methods and analysis:**

First, we conduct a qualitative study to explore factors contributing to antibiotic prescribing for UTIs in frail elderly, using semi-structured interviews with general practitioners, nursing staff, patients and informal caregivers. Next, we perform a pragmatic cluster randomised controlled trial in elderly care organisations. A multifaceted ASI is implemented in the intervention group; the control group receives care as usual. The ASI is centred around a decision tool that promotes restrictive antibiotic use, supported by a toolbox with educational materials. For the implementation, we use a modified participatory-action-research approach, guided by the results of the qualitative study. The primary outcome is the number of antibiotic prescriptions for suspected UTIs. We aim to recruit 34 clusters with in total 680 frail elderly residents ≥70 years. Data collection takes place during a 5-month baseline period and a 7-month follow-up period. Finally, we perform a process evaluation. The study has been delayed for 6 months due to COVID-19 and is expected to end in July 2021.

**Ethics and dissemination:**

Ethical approvals and/or waivers were obtained from the ethical committees in Poland, the Netherlands, Norway and Sweden. The results will be disseminated through publication in peer-reviewed journals and conference presentations.

**Trial registration number:**

NCT03970356.

Strengths and limitations of this studyThe qualitative study allows for a comprehensive analysis of the factors at play in decision-making on urinary tract infections in frail elderly, which is essential to make progress in antibiotic stewardship in this setting.The pragmatic approach with its diverse international setting offers both broad applicability of results in general practice and elderly care medicine, and gives a chance to evaluate country-specific outcomes.The use of participatory action research (PAR) embedded within a cluster randomised trial is infrequent, and may offer valuable insights for future trials; however, a limitation of the tailored approach is that the results will not be exactly replicable.The process evaluation of the PAR approach will provide guidance for implementation in daily practice, including a toolbox with supportive educational materials.The COVID-19 pandemic began in the midst of the implementation process, undoubtedly affecting the process and results.

We set out to evaluate whether a multifaceted ASI is effective in reducing antibiotic prescribing for UTIs in frail elderly in various long-term care settings (in Poland, the Netherlands, Norway and Sweden). To accomplish the substantial behavioural changes that are needed, we believe we need a combination of qualitative methods for exploration and a PAR approach for implementation. First, we perform a qualitative study with semi-structured interviews to develop a conceptual model of factors contributing to antibiotic prescribing decisions in this population. Then, we conduct a cluster RCT in frail elderly in care homes attended by general practitioners (GPs) using PAR to implement an ASI. Finally, we conduct a process evaluation.

### Objectives

Obtain insights into all relevant factors that contribute to antibiotic prescribing for UTIs in frail elderly.Develop a conceptual model integrating these identified factors to guide the development of ASI for UTIs in frail elderly.Study the effects of the implementation of a multifaceted ASI on antibiotic prescription rates for UTIs in frail elderly.Evaluate the implementation process to understand the cluster RCT outcomes, and the added value of the PAR approach to implement ASIs.

## Methods and analysis

The Improving antibiotic Prescribing for UTIs in frail elderly (ImpresU) study consists of a qualitative study and a cluster RCT. Their integration is shown in figure 1.

**Figure 1 F1:**
[figure not shown]
Schematic overview of the interplay between the two studies. The qualitative study offers insights to tailor the antibiotic stewardship intervention in the cluster randomised controlled trial (RCT), through a country-specific local analysis. The cluster RCT consists of a baseline and follow-up period for data collection, with an intervention period or usual care in between (the timeline is provided in figure 3). A process evaluation follows at the end of the cluster RCT. GP, general practitioner; UTI, urinary tract infection.

### Qualitative study

The aims are to explore all relevant factors that contribute to antibiotic (non-)prescribing for UTIs in frail elderly, and to integrate these into a conceptual model to guide the development of effective ASIs.

#### Design and setting

An exploratory qualitative study using semi-structured interviews is conducted in Poland, the Netherlands, Norway and Sweden. Interviews are conducted with representatives of three relevant stakeholder groups in the setting of elderly care at home and in institutions: (1) GPs, (2) nursing staff and (3) patients and informal caregivers.

#### Eligibility criteria, recruitment and sample size

Recruitment takes place through the networks of the research teams per country. We use purposive sampling to reach variation within the representatives of each stakeholder group (eg, in setting, years of experience for healthcare professionals). All participants need to be capable and willing to provide informed consent and communicate personal thoughts in the local language. Patients need to be 70 years or older, and are not recruited during the acute phase of a disease. The aim is to conduct approximately 60 interviews (ie, 15 per country), preferably equally distributed over the three stakeholder groups.

#### Data collection and management

Topic lists and interview guides are designed based on literature and (clinical) experience from the researchers.^6^ Pilot interviews are performed in each country to verify the appropriateness and completeness of the topic lists. All interviews are conducted in the native language and audio recorded. Basic demographic data (eg, gender, age) of participants are collected. Collected data and transcripts are pseudonymised, using a code for each participant.

#### Data analysis

Data are analysed with use of the framework method,^11^ which consists of the following steps: (1) interviews are transcribed verbatim and translated into English; (2) the researchers (re)read the interviews for familiarisation; (3) two researchers independently code a first batch of interviews; (4) through consensus, a preliminary framework is formed; (5) the remaining interviews are coded using the framework; additions and changes are discussed within the research team; (6) data are organised in a framework matrix; (7) data are interpreted, and a conceptual model of factors is derived from the matrix.

### Cluster RCT

The trial aims to evaluate whether a decision tool for restrictive antibiotic use, implemented using a PAR approach, reduces antibiotic prescribing for UTIs in frail elderly. For this report, we used the Standard Protocol Items: Recommendations for Interventional Trials reporting guidelines.^12^

#### Design and setting

A cluster RCT is performed in nursing homes in Poland, the Netherlands, Norway and Sweden, and in residential care homes and home care organisations in the Netherlands, attended by GPs. More details on the setting are provided in the online supplemental data 1. The cluster and unit of randomisation is the care organisation linked to the GP practice; one care organisation may be attended by multiple GP practices or vice versa. In the final months of the study period, a process evaluation is performed.

10.1136/bmjopen-2021-052552.supp1Supplementary data

#### Eligibility criteria and recruitment

Recruitment of clusters is performed through the networks of the research groups in Poland, the Netherlands, Norway and Sweden. The care organisations identify eligible patients, provide written study information, and ask whether they may be approached by the research team. Written informed consent from patients (or representatives in case of legal incapacity) is obtained by a visiting researcher or nurse.

For inclusion, patients need to be 70 years or older, have physical and/or mental disabilities and ADL dependency requiring care, do not use prophylactic antibiotics, do not receive hospice care and are estimated not to have a very limited life expectancy (≤1 month). Patients are excluded when they start prophylactic antibiotics, start receiving hospice care, have a limited life expectancy (≤1 month), pass away, or move away from the cluster. Patients need to be included for at least 2 months to contribute data to the study.

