#### Outcome assessments

##### Primary outcome measure

Number of prescriptions of antibiotics for suspected UTIs.

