##### Secondary outcome measures

Number of prescriptions of antibiotics for suspected UTIs in office hours.Number of incorrect prescriptions of antibiotics for suspected UTIs.Incidence of suspected UTIs.Incidence of complications within 21 days after each UTI suspicion (presence yes/no of a complication: delirium, pyelonephritis, sepsis and renal failure).Incidence of referral to a hospital within 21 days after each UTI suspicion.Incidence of hospital admission within 21 days after each UTI suspicion.Mortality.Mortality within 21 days after each UTI suspicion.All outcomes are assessed during the follow-up period, and expressed per patient-year.

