**Figure 3 F3:**
[figure not shown]
Timeline of the cluster randomised controlled trial. The periods of data collection and procedures are shown for the clusters and participating patients. CRF, case report form; UTI, urinary tract infection.

For each participant, a CRF with patient characteristics is filled in at study entry consisting of items concerning demographics, ADL dependency measured through the Katz Index of Independence in Activities of Daily Living,^23^ and relevant medical history. The GPs prospectively register each UTI suspicion on a short registration form, describing symptoms, diagnostics, and antibiotic treatment (primary and secondary outcomes). After 7 and 21 days, follow-up forms are filled in to assess the course of disease, any change in antibiotic treatment, complications, and mortality (primary and secondary outcomes). Overall mortality (secondary outcome) is registered on exclusion of a patient. Any missing data are retrospectively registered through consultation of GPs, nurses and/or access of the medical records.

Furthermore, anonymised data concerning COVID-19 incidence in the participating care organisations are registered during the follow-up period.

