#### Data analysis

The analysis will follow the intention-to-treat principle. For the primary outcome, a generalised linear mixed model for Poisson distributions will be used. In case the assumptions for Poisson distributions are insufficiently met, other distributions will be considered (ie, negative binomial, generalised Poisson, zero-inflated Poisson). A random intercept will be included to correct for clustering within care facility and/or GP, and an additional random intercept will be included to correct for repeated measurements in patients. When results indicate no or very low clustering at the facility/GP or patient level, the corresponding random intercept will be excluded from the analysis. The comparison between intervention and control group, estimated with the time by treatment interaction, will be reported as Rate Ratio’s with a 95% CI and a corresponding p value. In a second model, prespecified prognostic factors will be added: age, gender, ADL dependency, presence of an indwelling catheter, dementia, recurrent UTIs, diabetes mellitus, and kidney disorders. In case there are missing values on baseline variables that were selected as potential confounders, multiple imputation will be considered. Furthermore, subgroup analysis will be performed to assess outcomes in groups per country, with different gender, age, presence of dementia, urinary incontinence and indwelling catheter.

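### The 2-month minimum stay makes a resident's data depend on surviving and staying after inclusion, conflicts with unqualified intention-to-treat, and lowers the mortality rate among late entrants

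*Protocol article*

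**What the plan says.** The protocol article (Cluster RCT, Eligibility criteria and recruitment) lists the events that end a resident's participation. The list opens with "Patients are excluded when they start prophylactic antibiotics, start receiving hospice care" and goes on to short life expectancy, death and leaving the cluster. It then adds a minimum stay: "Patients need to be included for at least 2 months to contribute data to the study".

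The Data analysis section states: "The analysis will follow the intention-to-treat principle". It names no exception, no modified analysis set and no analysis that restores residents with short stays.

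The primary outcome is a count ("Number of prescriptions of antibiotics for suspected UTIs"). Under Secondary outcome measures, the scale is fixed for every outcome: "All outcomes are assessed during the follow-up period, and expressed per patient-year". Overall mortality and mortality within 21 days of a UTI suspicion are both secondary outcomes. The Data collection section adds: "Overall mortality (secondary outcome) is registered on exclusion of a patient".

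**The concern.** Whether a resident is analysed depends on what happens after inclusion. A resident who dies, enters hospice care, moves away or starts prophylaxis within 2 months of inclusion gives no prescriptions, no death and no person-time. A resident enrolled at the same time who stays gives all three, including 2 months in which death was impossible by construction. For residents enrolled after their cluster was allocated, this is a post-randomisation exclusion in an unblinded trial.

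Such residents are to be expected. The Discussion says that continuing deaths increase the need for new recruitment, and the Intervention section shows that the intervention had already begun before the 6-month pause. The sample-size section doubles the cluster size from 10 to 20 to cover loss to follow-up.

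Mortality is where it matters most. The intervention restricts antibiotics in frail people, and the section on participant safety provides for no data monitoring committee and no reporting of serious adverse events. The mortality outcomes therefore carry much of the safety evidence, and early deaths among new entrants would be missing from them.

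A minimum stay is not needed to handle unequal follow-up, because outcomes are already rates per patient-year.

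**Working it through.** **The plan's own figure.** The only related figure is the sample size. Inputs from the Sample size section: 0.75 and 0.40 prescriptions per year, 7 months, clusters of 10, intracluster correlation 0.06, one-sided alpha 0.05, power 0.80.

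- Mean counts: 0.75 × 7/12 = 0.4375 and 0.40 × 7/12 = 0.2333.
- Noether's formula for the Wilcoxon test with tie correction gives about 216.8 patients.
- The design effect is 1 + 9 × 0.06 = 1.54, so the total is about 334 patients and 34 clusters. The protocol gives 333 and 34.

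The figure reproduces and does not use the 2-month rule, so removing the rule leaves the required number unchanged.

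**Whom the rule reaches.** The 2 months are most naturally counted from inclusion. Someone enrolled in the first 3 months of the 5-month baseline meets the rule before baseline ends. Someone enrolled at the September 2020 restart has a 2- to 3-month intervention period before follow-up begins. For outcomes in follow-up, the rule therefore reaches residents enrolled less than 2 months before follow-up starts, or during it. The documents give neither their number nor an exit rate. As an outer bound, with an assumed annual exit of 10% to 40%, the share leaving within 2 months of entry is 1 − 0.90^(1/6) = 1.7% to 1 − 0.60^(1/6) = 8.2%. That is about 12 to 55 of 680 if every resident were exposed to the rule during follow-up, which is not the case.

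**Share of deaths discarded.** Assume a constant annual death hazard h. For entry at the start of follow-up, the share of 7-month deaths falling in the first 2 months is (1 − e^(−h/6)) / (1 − e^(−7h/12)).

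| h | Dead by 2 months | Dead by 7 months | Share discarded |
|---|---|---|---|
| 0.20 | 0.0328 | 0.1101 | 0.298 |
| 0.25 | 0.0408 | 0.1357 | 0.301 |
| 0.30 | 0.0488 | 0.1605 | 0.304 |
| 0.40 | 0.0645 | 0.2081 | 0.310 |

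The share hardly depends on h but depends strongly on entry date. With h = 0.30, entry 1 month before follow-up gives (1 − e^(−0.025)) / (1 − e^(−0.175)) = 0.154. Entry 2 months or more before gives 0. Entry 3 months into follow-up, if recruitment ran that long, gives (1 − e^(−0.05)) / (1 − e^(−0.10)) = 0.512 of the deaths in the remaining 4 months.

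**Effect on the mortality rate of those entrants.** Among residents retained from entry at the start of follow-up:

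- Expected deaths are E = 1 − e^(−5h/12).
- Expected person-time is 1/6 + E/h years.
- For h = 0.20: 0.0800 / (0.1667 + 0.3998) = 0.141 per year, 0.71 of the true rate.
- For h = 0.40: 0.1535 / (0.1667 + 0.3838) = 0.279 per year, 0.70 of the true rate.

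The rate in this subgroup is understated by about 30%. The whole-trial bias is diluted by the unknown share of such entrants.

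**Effect on the primary rate ratio.** A simulation assumed a control rate of 0.75 per year, gamma frailty variance 1.5, 25% annual exit, and a 10% to 50% chance of starting prophylaxis at each prescription from the second on.

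- No prophylaxis starts, and exit unrelated to outcome: the 2-month rule alone leaves the ratio unchanged.
- Both rules, true ratio 0.53: 0.53 to 0.57.
- Both rules, true ratio 1.00: about 1.00 when prophylaxis starts equally often in both arms, and 0.95 to 1.08 when the arms differ.

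**The case against.** Clusters are the randomised unit, and all can still be analysed as allocated. That stands, so the breach is at resident level. The visible text does not date randomisation relative to each inclusion (Figure 3 is not shown). For early enrolees, it therefore cannot be established that an early exit came after randomisation.

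Many residents will also pass the 2 months before outcome time begins. That stands too, and it means that the 30% figure belongs to one entry date and is not an estimate for the trial.

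Three stronger readings are tempting but unsupported.

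- **That starting prophylaxis erases a resident.** The protocol says "Patients are excluded when they start prophylactic antibiotics", and a reader might infer that frequent receivers of UTI prescriptions are removed with all their data. If 2% to 4% of residents had 3 prescriptions a year (assumption) and were deleted from one arm only, that arm's ratio to 0.75 would be 0.94 to 0.88. But death and moving stand on the same list, and mortality is registered at exclusion, so the word means leaving follow-up. Earlier data are kept once the stay has reached 2 months. With the same assumptions and censoring at the second prescription, such a resident contributes on average 0.304 + 2 × 0.522 = 1.348 prescriptions over 1.348/3 = 0.449 years. With 4% of such residents the arm's rate is (0.63 × 7/12 + 0.04 × 1.348) / (0.96 × 7/12 + 0.04 × 0.449) = 0.729, a ratio of 0.97. With 2% it is 0.740, a ratio of 0.99. This is potentially informative censoring, since unblinded prescribers make the decision. It also matches the entry criterion of no prophylactic use, and following residents beyond that point would be a debatable change of target.
- **That residents admitted with a life expectancy just above 1 month can never contribute.** Life expectancy is an estimate, and some will outlive it.
- **That the primary result is materially biased.** The simulation shows modest shifts, which under no true effect appear only if prophylaxis starts are assumed to differ by arm.

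**Conclusion.** The conflict is in the stated text: a rule that depends on survival and stay after inclusion sits beside an intention-to-treat declaration without exception. It is not a detail left to an analysis plan. The consequence is narrow but real. Early deaths and prescriptions among late entrants are lost, and the mortality rate is biased downwards. For entry exactly at the start of follow-up, about 30% of 7-month deaths are discarded, assuming a constant annual hazard of 0.2 to 0.4. The share falls to zero for residents enrolled at least 2 months earlier.

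The trial-wide size cannot be derived, because the documents give no number of late entrants and no exit rate. If mortality is equal in the two arms and late entry is similar, the comparison between arms need not be biased, but a difference confined to the first weeks after entry would not be seen. The effect on the primary rate ratio is probably small and of unknown direction. No stated figure in the protocol is wrong on this point.

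**What to change.** Delete the 2-month minimum from the primary analysis. Analyse every included resident, whatever the length of stay, with the log of observed person-time as offset. Count all deaths in the mortality outcomes. Report exits by reason and arm, with prophylaxis starts shown separately, so that informative censoring can be judged. Keep the 2-month restriction as a sensitivity analysis only.

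The cost is mainly protocol and analysis wording. Deaths are already registered when a resident leaves, and the Trial status section places database lock still ahead. The sample size does not change, and person-time can only increase. The downside is some very short follow-up times, which the offset handles.

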#### Randomisation and blinding

Clusters are randomised to intervention or usual care, using SAS software V.9.4 by an independent data manager.^19^ Block randomisation is used to assign clusters to intervention or control in each country, stratified on cluster size (small/medium/large). Due to the nature of the intervention, blinding is not possible; however, the aims of the study outcomes are not explicitly stated to the control clusters to avoid contamination.

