##### Implementation: modified PAR approach

The intervention is tailored based on an analysis of the interview data to identify country-specific barriers and facilitators. For example, the roles of the healthcare professionals and knowledge gaps in care for UTIs differ per country and need to be targeted accordingly. During the intervention period, the researchers and healthcare professionals together go through a cyclical process of reflection, planning and action during sessions for education and evaluation. These sessions combine a top-down and bottom-up approach; both education on the decision tool and any knowledge gaps identified in the qualitative study, as well as reflection and planning for local implementation. The aim is to go through at least two PAR cycles in each cluster, and to actively involve physicians as well as nursing staff. Further tailoring may be performed in each country and cluster locally.

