#### Data collection

Data are collected during a 5-month baseline period and a 7-month follow-up period, through case report forms (CRFs) completed by the GP, nurse or researcher based on contact with a healthcare professional or medical file. The timeline for participating clusters and participants is displayed in figure 3.

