#### Data management

Data are collected pseudonymised on paper forms, using a study code for each patient. Afterwards, they are electronically registered in the secured online database Research Online, according to regulations of the International Conference on Harmonisation - Good Clinical Practice. Research Online has multiple validation rules built into the eCRFs. The data cleaning process is supported by automatically and manually generated queries. At the end of the study, all data will be locked. Dedicated data sets are provided to the researchers for analysis. Data are kept securely for at least 15 years.

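### Blinding is ruled out for every role, with no masking of the analyst, while the primary model's distribution and random intercepts are to be chosen from the data without a stated criterion

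*Protocol article*

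**What the plan says.** All references are to the protocol article.

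- *Randomisation and blinding*: "Due to the nature of the intervention, blinding is not possible". No role is exempted. The one mitigation given is that "the aims of the study outcomes are not explicitly stated to the control clusters to avoid contamination", which concerns contamination and not analysis. Allocation is generated "using SAS software V.9.4 by an independent data manager".
- *Implementation: modified PAR approach*: during the intervention period "the researchers and healthcare professionals together go through a cyclical process of reflection, planning and action".
- *Data collection*: the case report forms are "completed by the GP, nurse or researcher based on contact with a healthcare professional or medical file".
- *Data management*: data are pseudonymised and locked at the end of the study. "Dedicated data sets are provided to the researchers for analysis". Neither a separate statistician nor coded arms are mentioned.
- *Data analysis*: the primary model starts as a Poisson mixed model. "In case the assumptions for Poisson distributions are insufficiently met, other distributions will be considered", with three alternatives named. On random effects: "When results indicate no or very low clustering at the facility/GP or patient level, the corresponding random intercept will be excluded from the analysis". Neither rule has a threshold. The treatment effect is the time-by-treatment interaction in this same model.

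**The concern.** The blinding statement is broader than its reason. An intervention made of joint sessions with staff cannot be hidden from staff or from those who lead the sessions. It can be hidden from a person fitting models to coded records. As worded, the article rules out a safeguard that remains available, and an analysis plan that masked the analyst would contradict it.

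This matters because of what is left open in *Data analysis*. Four distributions and the presence or absence of two kinds of random intercept give several candidate primary models, and the triggers are matters of judgement. The trigger for dropping an intercept is what the results show, and nothing says that those results are to be obtained without the treatment term. The outcome is a prescribing decision taken by unblinded clinicians, so the analysis is one of the few steps that can still be protected. If a model could have been chosen after its p value was seen, a positive result is easier to challenge.

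**Working it through.** **1. The plan's own figure.** The article gives no number for blinding or model choice. Its sample size shows how much clustering it expects. Inputs from *Sample size*: 0.75 and 0.40 prescriptions per patient-year, 7 months, one-sided alpha 0.05, power 0.80, intracluster correlation 0.06, 10 patients per cluster.

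- Mean counts: 0.75 × 7/12 = 0.4375 and 0.40 × 7/12 = 0.2333.
- Wilcoxon (Noether) total with tie correction on Poisson counts: 216.75 patients.
- Design effect: 1 + (10 − 1) × 0.06 = 1.54.
- 216.75 × 1.54 = 333.8, against 333 stated, and 333/10 = 33.3, so 34 clusters.

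The figure reproduces. The design therefore expects clustering to raise the variance by 54%, and yet the analysis may drop the cluster term without a criterion. Masking the analyst changes neither 333 nor 34.

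**2. Which roles the stated reason covers.**

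| Role | Does the intervention itself reveal the arm? | Masking provided |
|---|---|---|
| GPs and nurses | Yes, in intervention clusters | Aims not made explicit to control clusters |
| Researchers running sessions | Yes | None |
| Whoever analyses the locked set | No | None |

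**3. A simple bound.** Suppose a naive Poisson model is used where the true variance is larger by a factor φ. The two-sided type I error is then 2 × (1 − Φ(1.96/√φ)).

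- φ = 1.2 gives 7.4%.
- φ = 1.3 gives 8.6%.
- φ = 1.5 gives 11.0%.

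The φ values are assumptions. The planned model has random intercepts that would absorb part of the extra variance, so these are not error rates of the written plan.

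**4. Null simulation.** There were 1000 runs per setting, with 34 clusters and a mean of 0.4375 per patient. The assumed between-patient SD was 0.5 on the log scale. The test was two-sided at 0.05 on follow-up data only. A cluster-robust standard error with t on 32 df stood in for the random intercept. The Monte Carlo standard error at 5% is √(0.05 × 0.95/1000) = 0.7 percentage points. Rejection rates in %:

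| Patients per cluster | Assumed cluster SD (log) | Cluster term kept | Poisson, no cluster term | Negative binomial, no cluster term | Smallest p of the three | Fixed rule |
|---|---|---|---|---|---|---|
| 10 | 0.2 | 5.2 | 8.5 | 6.3 | 8.7 | 5.1 |
| 10 | 0.4 | 4.8 | 14.2 | 9.9 | 14.3 | 4.7 |
| 20 | 0.2 | 5.1 | 10.0 | 8.1 | 10.1 | 5.9 |
| 20 | 0.4 | 5.9 | 22.7 | 18.3 | 22.7 | 6.2 |

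The fixed rule keeps the cluster term if the estimated intracluster correlation exceeds 0.02, and otherwise chooses between Poisson and negative binomial on dispersion (cut-off 1.1).

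**5. Reading the table.** Taking the smallest p value adds at most 0.2 points to Poisson without the cluster term (8.7 − 8.5). Nearly all the inflation comes from losing that term. A rule fixed in advance stays near 5% even with the arm known. Masking and a criterion therefore do different work: masking stops a choice made for its result, and a criterion stops a poor model being chosen in good faith.

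**6. Limit.** The planned estimate is a time-by-treatment interaction that uses baseline data. Cluster differences that are stable over time partly cancel from such a contrast, so the effect of dropping the intercept could be smaller than shown, or of a different sign. The simulation shows that the choice can matter, not by how much in this trial.

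**The case against.** The strongest case against the point has five parts.

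- **Who analyses, and what they see.** A reader might infer that those who run the sessions choose the model with the arm in view. The article does not say so. The link is the shared word researchers in two sections, in a four-country consortium with several research groups, and nothing states that the arm label is visible in the analysis data sets. This objection stands, and the stronger reading is not made here.
- **Analysis-plan material.** Analyst masking and selection thresholds are often settled in a statistical analysis plan, which is not shown. This stands as far as silence goes. It does not cover a positive statement that blinding is impossible, or a written rule that drops an intercept on what the results show. The second half of the blinding sentence concerns control clusters, so the authors may have meant only clusters and staff. If so, the wording should say that.
- **Size.** The 7.4% to 11.0% figures might be read as the trial's type I error. They are the error of a naive Poisson analysis under assumed overdispersion, and the plan intends to leave Poisson when it does not fit. This stands.
- **Masking is neither necessary nor sufficient.** A fixed rule held 4.7% to 6.2% with the arm known, and a masked analyst could still drop the cluster term wrongly. This stands, and the fix therefore has two parts.
- **Imputation and coding.** Multiple imputation is tied to baseline covariates, which enter the second, adjusted model and not the first primary model. Forms already completed by unmasked staff cannot be protected by masking an analyst. Both stand.

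**Conclusion.** The point holds in a limited form. The article declares blinding impossible for a reason that does not reach the analyst and provides no analyst masking. It leaves the primary model's distribution and random intercepts to be decided from the data without a criterion. These choices may therefore be made with the effect in view. The article does not establish that they will be, or that session researchers will make them.

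The size is not determined by the documents. Under the assumed variance components, with follow-up data only, the candidate models span rejection rates from 4.8% to 22.7% under the null, and most of that span comes from omitting the cluster term. These figures are illustrative. The weakness is real and can be corrected, and it does not invalidate the trial. It should be settled before the unmasked analysis. *Trial status* puts database lock in September 2021, after the trial's expected end in July 2021.

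**What to change.** 1. In *Randomisation and blinding*, limit the statement to GPs, nursing staff and the researchers who deliver the intervention, and add that the analyst is masked until the primary model is fixed.
2. Have the independent data manager release a data set with anonymous cluster codes and the arm removed or permuted. Random intercepts need only a cluster code. With the arm removed, a true effect would appear as extra between-cluster variation or dispersion, which errs towards keeping the cluster term.
3. On that set, fix and sign the distribution, the random-effects structure and any central classification of incorrect prescriptions before the arm code is released.
4. In *Data analysis*, keep the cluster random intercept whatever its estimated size, or state the numerical criterion for dropping it. State likewise what counts as Poisson assumptions being insufficiently met.

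The cost is small but not zero: one masked export, prepared by someone outside the session team, and a short sign-off before the unmasked analysis. The article names an independent data manager for randomisation but does not say who prepares the analysis sets, so that role needs to be assigned. Sample size, power and trial procedures do not change. Coding already done by unmasked care staff remains unprotected.
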